### Analysis

#### Quantitative data analysis.

Descriptive statistics will be used to summarise characteristics of the eligible population and study population at baseline, recruitment and retention rates, satisfaction and understanding of test results and consultations, healthcare utilisation, and intention to change behaviour overall and by risk group. Means and standard deviations will be used for normally distributed continuous variables, medians and interquartile range for non-normally distributed continuous variables, and numbers and percentages for categorical variables. Where reported, all proportions and differences in proportions will be presented with 95% confidence intervals.

#### Uptake of breast cancer risk assessment.

Logistic regression will be used to assess the participant level characteristics associated with completion of the risk assessment amongst those consenting to the study, reporting both unadjusted and adjusted odds ratios (OR) with 95% confidence intervals. Chi-squared tests will be used to compare the proportions of those invited who take up the offer of breast cancer risk assessment between demographic subgroups using aggregate data from each participating practice. Test significant at p < 0.05 will be presented as statistically significant.

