### Design and setting

The study is a pragmatic multicentre feasibility study taking place in 5–8 GP practices in Cambridgeshire and Peterborough, England, UK. Fig 1 shows the study schedule (SPIRIT).

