### Processes and interventions

#### Practice recruitment.

GP practice recruitment was supported by the Clinical Research Network (CRN) Eastern. They approached practices across Cambridgeshire and Peterborough that refer patients at increased risk of developing breast cancer to the clinical genetics service at the Cambridge University Hospital NHS Foundation Trust. Practices were recruited from different areas to maximise participant sociodemographic and ethnic diversity. Practices that agree to take part signed a practice agreement form. Reasons for practices declining to take part in the study were collected where possible.

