#### The quantity of self-reported data using MyCanRisk.

The amount of information completed for non-family history risk factors alongside the number of family members reported in the pedigree will be summarised using descriptive statistics. Chi-square tests will be used to assess differences in the amount of information provided between demographic subgroups.

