#### Psychological and behavioural impact of multifactorial breast cancer risk assessment.

For continuous outcomes (anxiety, worry, risk perception, recall of risk information, and intentions) analysis of covariance will be used to calculate change at each follow-up within each risk group, adjusting for clustering between each GP practice. Any differences between the risk groups on analysis of covariance will be tested using an F-test, followed by estimation of the comparison between those at near population level risk and those at moderate or high risk based on the CanRisk assessment. All models will be adjusted for age, ethnicity, education level, deprivation, baseline EQ-5D and general practice. The size of the change between groups will be interpreted by comparison with the standard deviation (SD), with the criteria for clinically relevant change being a change of 0.5 SD [29]. We will also test for interactions between the risk groups and age, family history of breast cancer, numeracy, beliefs about breast cancer, time orientation, intolerance of uncertainty and responding “not anxious or depressed” versus “slightly/moderately/severely or extremely anxious or depressed” on EQ-5D at baseline. Analyses will be repeated within the subgroups where the p value for interaction is < 0.05.

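### The MyCanRisk data-quantity tests have no place for general practice, and the adjusted completion model does not say whether it includes practice, although the psychological models adjust for it (minor)

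*Protocol article*

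**What the plan says.** Three analysis sections of the Protocol article treat practice differently.

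- **Uptake of breast cancer risk assessment** (completion among consenters): "Logistic regression will be used to assess the participant level characteristics associated with completion of the risk assessment amongst those consenting to the study". Odds ratios are to be given both crude and after adjustment. The adjustment variables are not listed, and neither practice nor clustering is mentioned. A separate chi-squared comparison of uptake among those invited is made "using aggregate data from each participating practice"; it is not part of this point.
- **The quantity of self-reported data using MyCanRisk**: "Chi-square tests will be used to assess differences in the amount of information provided between demographic subgroups". No stratification or adjustment is given.
- **Psychological and behavioural impact**: the analysis of covariance is done "adjusting for clustering between each GP practice", and "All models will be adjusted for age, ethnicity, education level, deprivation, baseline EQ-5D and general practice". That last sentence stands under the psychological heading and includes baseline EQ-5D, so it reads as covering those models only.

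Two design statements bear on this. The study runs in "5–8 GP practices in Cambridgeshire and Peterborough" (Design and setting). Under Practice recruitment, "Practices were recruited from different areas to maximise participant sociodemographic and ethnic diversity".

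**The concern.** A comparison between demographic groups that pools women over practices mixes two contrasts: between groups inside a practice, and between practices with different populations. If practices differ both in who their patients are and in how much data those patients supply, the pooled test attributes part of the second contrast to the demographic characteristic. Because it also treats women as independent, its p-value is too small. With only 5–8 practices, chance differences between them do not average out.

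Demographic differences between practices are made likely by the recruitment strategy. Differences in a related outcome are anticipated, since Aims and objectives includes estimating how uptake varies between practices. What is at stake is the description of which groups do not finish the assessment and which give thin pedigrees. A problem located in a practice and a problem located in a demographic group call for different responses.

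**Working it through.** **Inputs from the Protocol article:** 1,000 consenters and 80% completion (Sample size); 5–8 practices (Design and setting); significance at p < 0.05 (Uptake section).

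**Assumed, because the documents give no figure:** the outcome ICC across practices (ρy), the ICC of the demographic characteristic across practices (ρx), equal practice sizes, and no true effect within practices. The 80% rate is stated for completion; using it for a MyCanRisk item is also an assumption.

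**1. The plan's own figure.** Half-width for completion: 1.96 × √(0.80 × 0.20 / 1,000) = 0.0248. This reproduces the stated ±2.5%. It is a simple binomial figure pooled over practices, with no allowance for clustering. This point does not dispute it.

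**2. The mechanism, in an aligned example.** Take five practices of 200 with deprived shares of 10, 30, 50, 70 and 90%, and completion of 90, 85, 80, 75 and 70% regardless of deprivation.
- Deprived: 200 × (0.1×0.90 + 0.3×0.85 + 0.5×0.80 + 0.7×0.75 + 0.9×0.70) = 380 of 500, or 76%.
- Not deprived: 800 − 380 = 420 of 500, or 84%.
- Crude OR = (380 × 80)/(120 × 420) = 0.60. Chi-square = 1,000 × (380×80 − 120×420)² / (500 × 500 × 800 × 200) = 10.0, p = 0.0016. The within-practice OR is 1.
- With completion running only from 85% to 75%, the counts are 390 v 410 of 500, OR 0.78, chi-square 2.5, p = 0.11.

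**3. Rough size when composition and outcome vary independently.** The variance of the crude contrast is inflated by about 1 + (m − 1)ρyρx, where m is women per practice. The error rate is then about 2[1 − Φ(1.96/√inflation)]. With ρx = 0.2:

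| ρy | 5 practices (m = 200): inflation, error | 8 practices (m = 125): inflation, error |
|---|---|---|
| 0.01 | 1.398, 9.7% | 1.248, 7.9% |
| 0.02 | 1.796, 14.4% | 1.496, 10.9% |
| 0.05 | 2.990, 25.7% | 2.240, 19.0% |

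The formula tends to overstate the error with so few practices, so simulation is the better guide.

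**4. Simulation, ICCs on the observed scale** (Beta-distributed practice rates; characteristic prevalence 40%; ρx of 0.05, 0.1 and 0.2; 5, 6 and 8 practices). The unstratified error is about 5–9% at ρy = 0.01 and 5–12% at ρy = 0.02. At ρy = 0.05 it is 8–9% with ρx = 0.05, 11–13% with ρx = 0.1, and about 18–21% with ρx = 0.2. With practice stratified or as a fixed effect it is 4–6% throughout.

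**5. Simulation, outcome ICC on the logit scale** (4,000 replicates per cell; crude chi-square against practice-stratified Mantel-Haenszel):

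| Practices, deprived share | ICC 0.01 | ICC 0.02 | ICC 0.05 |
|---|---|---|---|
| 5, 30–70% | 6.4% | 6.6% | 9.8% |
| 5, 10–90% | 9.7% | 12.7% | 24.1% |
| 8, 10–90% | 7.2% | 9.9% | 15.1% |

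With equal shares across practices the crude test holds its level (5.0–5.7%). With an outcome ICC of zero it is 5.1–5.4% whatever the shares. The stratified test stays at 4.4–5.9% throughout.

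The 24.1% lies above the step 4 maximum because a 10–90% spread over five practices is more extreme than ρx = 0.2: its variance is 0.08, and 0.08/0.25 = 0.32. The two outcome ICC scales also differ. An ICC of 0.05 is a practice SD of √(0.05 × 0.8 × 0.2) = 0.089 on the observed scale. On the logit scale it is √(0.05/0.95 × π²/3) = 0.416, or about 0.416 × 0.16 = 0.067 in completion.

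**The case against.** **The completion model may already include practice.** A reader might infer that the logistic regression ignores practice. The document does not say so: it promises adjusted odds ratios and leaves the covariates unnamed, as a condensed article may. This objection stands, so the completion model needs only a clarification. The data-quantity section is different, because it names a method that has no place for practice.

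**A practice effect on these outcomes may be small.** Consent, the baseline questionnaire and MyCanRisk are online, saliva kits are posted, and the research team produces the risk estimate. The stated objective about between-practice differences concerns uptake and risk distribution, not completion after consent or pedigree size. This stands too: an outcome ICC near zero is plausible, and the error is then near 5%.

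**Not every practice difference becomes a demographic effect.** A reader might infer that it does. It happens only where practice outcome and practice composition line up, by chance or otherwise. The recruitment statement shows an aim of diversity but gives no spread between practices.

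**The pooled association is a legitimate descriptive target.** If practices differ because their populations differ, a practice term removes part of a real gradient. This stands in part. It is a reason to report crude figures alongside the adjusted ones, and to keep practice out of the unadjusted model, which would otherwise no longer be unadjusted.

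**The consequences are limited.** A reader might infer that a false subgroup result would misdirect the pathway. Sample size instead ties adaptation to missed progression criteria and to process-evaluation data, which include interviews with women who do not complete the assessment. No progression criterion uses these tests.

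**Conclusion.** The point holds as a minor improvement. The firm part is the MyCanRisk section, which fixes unstratified chi-square tests while the psychological models for women in the same practices adjust for practice. The softer part is that the adjusted completion model does not say whether practice is included.

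The size cannot be derived from the documents, which give neither an ICC nor the demographic spread by practice. Under the observed-scale ICCs assumed above, the error at nominal 5% is about 5–9% at an outcome ICC of 0.01, 5–12% at 0.02, and up to about 20% at 0.05 with a characteristic ICC of 0.2. The last is an extreme corner, and a wider spread such as 10–90% over five practices could go somewhat higher. With balanced practices or an outcome ICC near zero there is essentially no inflation. All these figures assume 1,000 women; a MyCanRisk analysis confined to completers (1,000 × 0.80 = 800) would have fewer women per practice and less inflation.

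**What to change.** - **The quantity of self-reported data using MyCanRisk:** replace the chi-square tests with practice-stratified Mantel-Haenszel tests, or logistic regression with practice as a fixed effect, for whether an item is present. Use a count regression with practice as a fixed effect for the number of relatives in the pedigree.
- **Uptake of breast cancer risk assessment:** name general practice as a fixed effect in the adjusted logistic model of completion only. Keep the unadjusted odds ratios as descriptive figures. With 5–8 practices, a fixed effect is safer than a random effect or cluster-robust standard errors.
- **Reporting:** show crude subgroup figures beside the practice-adjusted ones in both sections.

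The cost is a sentence or two of wording and 4–7 degrees of freedom (number of practices minus one). Practice is known for every participant, so no new data are needed. The adjusted estimates become within-practice contrasts and will be somewhat wider for characteristics that vary mainly between practices; hence the crude figures alongside.

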#### Participant recruitment.

Eligible women are identified through searches of the electronic health records at General Practices based on the inclusion and exclusion criteria above. To prevent including women who may reach the age of 50 years between the searches being completed and receiving the invitations (see ‘Processes and Interventions’ section below), the search includes women aged 40–48 years. Depending on the population size of each practice, recruitment rate, and overall uptake into the study, either all or a random sample of those women who meet the eligibility criteria are invited to take part in the study. Invitations are staggered in random order. Those women are sent an invitation letter and S3 Participant information sheet by post. A reminder letter is sent by post two to four weeks later to those women who have not completed the consent form.

Women can complete the online written consent form which includes a screening question about breast cancer susceptibility gene already identified within their family. Those answering yes to this screening question are advised to make an appointment to discuss their breast cancer risk with their GP and are not able to continue with the study. After providing online written consent, all participants are asked to complete a short baseline questionnaire (details below) hosted online. On completion of the baseline questionnaire, participants are asked to provide data for a breast cancer risk assessment.

Recruitment opened on the 28^th^ of November 2024 for a duration of 8 months (until the 30^th^ of June 2025) or until 1,000 women have been recruited, whichever happens first.

Participant recruitment and flow through the study is summarised in Fig 2.

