
### Data collection

The data collection process is shown in Fig 2.

Participant baseline data is collected via an online questionnaire.

Participant level follow-up data is collected via participant questionnaires at 1, 3 and 6 months after receiving the results letter and from the GP electronic medical records 6 months after the last participant has received the results letter for all individuals who have consented to participate in the study. This includes coded entries relating to breast symptoms, breast cancer risk and, for those at moderate and high risk, uptake of risk-reducing interventions.

Practice-level aggregated data on the age, ethnicity and Index of Multiple Deprivation of all eligible women will be extracted at the end of the study from the GP electronic medical records. Practice-level and aggregated individual level data on the number of referrals of women potentially at above population-level risk for breast cancer and the outcomes of those referrals for all practices across Cambridgeshire and Peterborough for the period of the study will also be extracted from the electronic health records at the clinical genetics clinic at Cambridge University Hospitals NHS Foundation Trust. For the practices participating in this study, the same data will be extracted for the 12 months prior to the study. Data on the number of women registered at each practice will be extracted from publicly available National General Practice profiles.

A mixed-methods process evaluation is being conducted alongside collection of outcome data to explore how proactive breast cancer risk assessment is delivered and perceived at practice and patient levels. The main four questions guiding this element of the study will focus on: 1) whether this feasibility study did what it was set out to do; 2) whether the different elements in the study design worked and why; 3) what the different stakeholders thought about CanRisk and how it was implemented in general practice: and 4) whether implementing CanRisk in general practice is acceptable. Data is collected from women, GPs conducting breast cancer risk consultations, and practice managers and/or research leads from the different research sites. Three sources of data contribute to this process evaluation.

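### Uptake by demographic subgroup: the only demographic counts described do not match the invited denominator, and the chi-squared test as named takes no account of practice

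*Protocol article*

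**What the plan says.** The analysis section on uptake of risk assessment states: "Chi-squared tests will be used to compare the proportions of those invited who take up the offer of breast cancer risk assessment", and continues "between demographic subgroups using aggregate data from each participating practice". It adds: "Test significant at p < 0.05 will be presented as statistically significant". Neither stratification by practice nor a practice term is mentioned for this test. By contrast, the section on psychological and behavioural impact adjusts its models for general practice.

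Under Data collection, the one aggregate demographic extract described is this: "aggregated data on the age, ethnicity and Index of Multiple Deprivation of all eligible women will be extracted at the end of the study". Under Participant recruitment, depending on practice size, recruitment rate and overall uptake, "either all or a random sample of those women who meet the eligibility criteria are invited to take part in the study".

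The study is "taking place in 5–8 GP practices in Cambridgeshire and Peterborough". Under Practice recruitment: "Practices were recruited from different areas to maximise participant sociodemographic and ethnic diversity". One specific objective is to estimate between-practice differences in uptake, to inform a future cluster-randomised trial.

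**The concern.** There are two separate weaknesses.

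**Denominator.** The test needs the age, ethnicity and deprivation of the invited women, by practice. The article describes counts for eligible women only. The two sets coincide if everyone eligible is invited and the list does not change, but the recruitment section allows otherwise. It also makes the decision to sample depend on practice size and recruitment rate, so the sampling fraction can differ by practice.

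**Practice.** If practices differ both in uptake and in demographic make-up, a pooled chi-squared test assigns part of the practice difference to the subgroup. Recruiting practices for diversity makes differing make-up likely, and differing uptake is something the study sets out to measure.

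At stake is the answer to who takes up the offer. It bears on the design of the later trial, and the introduction raises inequality as a reason for a proactive approach.

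**Working it through.** **The plan's own figure.** No precision or power is given for the subgroup tests. The nearest figure is the uptake precision in the Sample size section, ±1.1% at 20%. The half-width is 1.96 × √(p(1−p)/n).
- n = 5,000: 1.96 × √(0.20 × 0.80 / 5,000) = 1.11%. This reproduces the figure.
- n = 5,000/8 = 625: 1.96 × √(0.20 × 0.80 / 625) = 3.1%.

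The stated figure therefore needs all invitees pooled with practice ignored, although the text attaches it to each practice. The same sentence expresses uptake per eligible woman, whereas the outcome list and the analysis express it per invited woman.

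**Denominator illustration** (sizes, fractions and shares are assumptions). Five practices have 1,000, 1,000, 1,000, 1,500 and 2,000 eligible women. Sampling fractions are 1, 1, 1, 2/3 and 1/2, so 1,000 are invited in each. The subgroup's share is 10, 20, 30, 40 and 50%. True uptake is 20% of invitees everywhere.
- Subgroup: invited 100 + 200 + 300 + 400 + 500 = 1,500, takers 300, eligible 100 + 200 + 300 + 600 + 1,000 = 2,200.
- Others: invited 3,500, takers 700, eligible 900 + 800 + 700 + 900 + 1,000 = 4,300.
- On invited counts: 300/1,500 = 20% against 700/3,500 = 20%.
- On eligible counts: 300/2,200 = 13.6% against 700/4,300 = 16.3%, chi-squared 7.8, p about 0.005.

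The gap vanishes (chi-squared 0) if everyone is invited, if the sampling fraction is the same everywhere, or if case-mix is the same everywhere. A common fraction of 80% only lowers the level from 20% to 16% in both groups.

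**Practice illustration** (assumed values, correct invited counts). Five practices invite 1,000 each, with uptake 28, 24, 20, 16 and 12%, subgroup share 10, 20, 30, 40 and 50%, and no difference within any practice.
- Subgroup: (28 + 48 + 60 + 64 + 60)/1,500 = 260/1,500 = 17.3%.
- Others: (252 + 192 + 140 + 96 + 60)/3,500 = 740/3,500 = 21.1%.
- Pooled chi-squared: 5,000 × (260 × 2,760 − 1,240 × 740)² / (1,500 × 3,500 × 1,000 × 4,000) = 9.5, p about 0.002.

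This example aligns uptake and share perfectly, so it is a strong case.

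**Simulation with milder assumptions.** There were 4,000 runs with 5,000 invited in equal practices. Practice uptake was drawn around a mean of 20% and subgroup share, independently, around 30%. There was no subgroup effect within practice. Type I error of the pooled chi-squared test at nominal 5%:

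| Practices | Uptake SD (points) | Share SD 10 points | Share SD 20 points |
|---|---|---|---|
| 5 | 2 | 6.1% | 8.6% |
| 5 | 4 | 9.7% | 20.2% |
| 5 | 6 | 14.8% | 29.7% |
| 8 | 2 | 5.5% | 7.9% |
| 8 | 4 | 7.8% | 14.4% |
| 8 | 6 | 11.9% | 24.0% |

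If either SD is zero, the pooled test stays at about 4–6%. The practice-stratified Cochran-Mantel-Haenszel test gives 4.3–5.6% in every scenario. The simulation error near 5% is √(0.05 × 0.95/4,000) = 0.34 points, so the 5.5% cell cannot be told apart from 5%.

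**The case against.** The analysis section names the right denominator, the invited women. The eligible-women extract is never said to feed this test, and the descriptive analysis gives it another use, to summarise the eligible population. A random sample preserves each practice's composition in expectation. The wording about aggregate data from each practice is compatible with a stratified test, and an analysis plan that is not shown could specify one. A crude difference is also a true description of who took up the offer. Stratifying answers a narrower question and may remove part of a real area-level deprivation gradient. Overall uptake of 16%, not this test, is the progression criterion, and confidence intervals are promised for all proportions and differences.

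Most of this stands as a limit on the claim. What it does not answer is that the article describes no source for invited counts by subgroup while allowing sampling, and that it names a plain test and attaches a significance statement to it.

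Some stronger readings are tempting but unsupported:
- That the plan states a wrong denominator. It does not; the use of eligible counts is an inference from the only extract described.
- That ageing makes the end-of-study list badly unrepresentative. Search dates are not given, and eligibility runs to 49 while the search stops at 48, so a woman aged 48 at search is still in range a year later. The article does not allow any net effect on subgroup contrasts to be calculated.
- That practice distorts every demographic contrast. This is not shown, notably for age within so narrow a band.
- That the logistic model for completion omits practice. Its covariates are not listed.

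**Conclusion.** The concern holds in a limited form. The passages on invitation, data extraction and analysis do not agree on whose demographics form the denominator. Eligible counts would bias subgroup comparisons if sampling fractions and case-mix both vary by practice, or if the list changes differently between subgroups. The gap of 13.6% against 16.3% shows that this can matter; it does not predict what will happen.

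Separately, the test as named does not protect its p-values against practice effects. Type I error is about 6–9% for an uptake SD of 2 points and 8–20% for 4 points, over 5 or 8 practices and share SDs of 10–20 points. The document gives none of these SDs, and the inflation needs both uptake and case-mix to vary. A reader might infer that a pooled difference would be false. It would be correct as a crude description; the error lies in reading its p-value as evidence of a subgroup effect apart from practice.

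This is a secondary analysis in a feasibility study. The point is worth correcting, but it does not threaten the study's main conclusions.

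**What to change.** 1. Reconcile the Participant recruitment, Data collection and uptake analysis sections on one denominator. State that age, ethnicity and deprivation counts come from each practice's invitation list, taken at the time of search or invitation. If all eligible women are invited at a practice, say so.
2. Report crude uptake by subgroup, with confidence intervals, as description.
3. Base the p < 0.05 comparison on a Cochran-Mantel-Haenszel test stratified by practice, or on grouped-data logistic regression with practice as a term.

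The cost is wording, an aggregate count on lists that the invitation process already requires, and a little more analysis. The stratified result describes differences within practices and can remove part of an area-level gradient, so it should stand beside the crude figures and not replace them.
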